## Abstract

**Introduction:** India is in the process of a major epidemiological transition towards non-communicable diseases. Cardiovascular disease (CVD) is the leading cause of death in women in India. Predisposing independent risk factors include pregnancy-related conditions, e.g., hypertensive disorders of pregnancy (HDP) and gestational diabetes (GDM) - also associated with significant perinatal mortality and morbidity. Early identification, referral and management of pregnant women at increased risk of future CVD may offer opportunities for prevention. In rural India, Community Health Workers (CHWs) provide most antenatal and postnatal care. Innovative solutions are required to address integrated care for rural women during transitions between antenatal, postnatal and general health services. The George Institute's SMARThealth Programme has shown that CHWs in rural India screening non-pregnant adults for cardiovascular risk, using a decision support system, is feasible. Building on this, we developed a targeted training programme for CHWs and a complex system-level intervention that uses mobile clinical decision support for CHWs and primary care doctors to screen high-risk pregnant women. In addition to addressing HDP and GDM, the intervention also screens for anaemia in pregnancy.

**Methods/Design:** A pilot study will be undertaken in two diverse rural districts of India: Jhajjar (Haryana) and Guntur (Andhra Pradesh). Two Primary Health Centre clusters will be randomised to intervention or control groups at each study site. The primary objective of this pilot study is to explore the feasibility and acceptability of the SMARThealth Pregnancy intervention. Secondary objectives are to estimate: (a) prevalence rates of moderate to severe anaemia, HDPs and GDM at the study sites; (b) referral and follow-up rates, and (c) mean haemoglobin and blood pressure values at the routine 6 week postnatal visit. A process evaluation will be conducted to explore the acceptability of the SMARThealth Pregnancy intervention for pregnant women and healthcare workers using qualitative methods.

**Discussion:** It is anticipated that the findings of this pilot study will help determine the feasibility and acceptability of the SMARThealth Pregnancy intervention, and highlight how the intervention might be further developed for evaluation in a larger, cluster randomised controlled trial.

**Clinical Trial Registration:**
www.ClinicalTrials.gov, identifier: NCT03968952.

## Introduction

Cardiovascular disease (CVD) is the leading cause of death in women in India (1), and the prevalence of cardiometabolic disorders is rising (2). Two-thirds of the Indian population live in rural areas (3), where lack of health education and access to health services make women less likely to seek care for cardiometabolic disorders. Pregnancy-related conditions including hypertensive disorders of pregnancy (HDP) and gestational diabetes mellitus (GDM) carry independent risks for future CVD in women (4–8). Early identification, referral and management of pregnant women at increased risk of future cardiometabolic disorders may offer opportunities for prevention. Innovative solutions are required to address the needs of rural women, particularly during the transitions between antenatal and postpartum care and adult health services.

Community Health Workers (CHWs) known as Auxiliary Nurse Midwives (ANMs) and Accredited Social Health Activists (ASHAs) in rural India, provide the majority of antenatal and postnatal care. Task-sharing with CHWs and use of digital and mhealth interventions in rural India have been shown to facilitate the detection, referral and management of non-communicable diseases (NCDs) in non-pregnant adults (9, 10), and HDP in pregnant women (11). There is, however, a paucity of high-quality evidence to guide the postnatal management of women following high-risk pregnancy, including those with multi-morbidity in low-resource settings. Most randomised trials in the postnatal period have focused on neonatal outcomes (12, 13), rather than focus on women - who remain at risk of both immediate complications and future cardiometabolic disorders.

We conducted an in-depth contextual study in rural areas of two diverse states in India (Haryana and Andhra Pradesh) exploring women's and healthcare professionals' understanding of high-risk conditions in pregnancy and their sequalae during and after pregnancy (14). The study highlighted that anaemia in pregnancy was considered as a priority area for high-risk pregnant women by healthcare workers and government officials. We further identified the need for education to improve awareness and institution of standardised screening to identify women with pregnancies complicated by HDP and GDM, and institute a regular follow up schedule. This contextual study provided the foundation for the theory-informed development of a complex intervention (SMARThealth Pregnancy), consisting of mobile clinical decision support, and a targeted education and training programme for CHWs. The focus of the SMARThealth Pregnancy intervention is to address improvement of women's postpartum health, through provision of clinical decision support and training to CHWs in relation to three priority areas: Anaemia, HDP and GDM, during the crucial transition between antenatal and postnatal care, and general health services. The intervention aims to connect pregnant women identified to be at high risk of future cardiometabolic disorders to the Government of India's non-communicable disease (NCD) programme for ongoing, life-long follow-up. The intervention is informed by behaviour change theory (15–17) and the MRC framework for complex interventions (18).

The underlying hypothesis of this pilot study is that the SMARThealth Pregnancy intervention can improve the detection, referral and management of anaemia, HDP, and GDM during the antenatal and postnatal period; and improve knowledge of CHWs to enable them to manage high-risk pregnancies in two areas of rural India. We aim to develop sufficient evidence to design a larger trial that would test the effectiveness of the intervention on an adequate scale.

### Aims and Objectives

The aim of this pilot study is to assess address the feasibility and acceptability of the SMARThealth Pregnancy intervention; determine whether the intervention integrates within the existing health system, and identify any unintended consequences.

The primary objectives of the study are to:

Determine whether it is feasible to recruit clusters of Primary Health Centres (PHCs) and pregnant women to the study.Evaluate the intervention's acceptability to end-users (including CHWs and pregnant/postpartum women), to ensure the proposed intervention is feasible and optimised for a definitive trial.

The secondary objectives include:

Determine prevalence rates of moderate to severe anaemia, HDP and GDM in pregnant women at the study sites.Determine referral rates for these conditions.Determine loss to follow-up rates up to 6 weeks postpartum.Assess the extent to which the intervention was delivered as planned by CHWs (intervention fidelity) by looking at the completeness of the entries into the mHealth tablet and the timing of these entries.Collection of clinical outcome data, including mean blood pressure (BP) and haemoglobin (Hb) levels at 6–10 weeks postpartum, to inform a sample size calculation and intraclass correlation coefficient (ICC) required for a larger cluster randomised controlled trial (cRCT).To assess CHWs' (ANMs and ASHAs) knowledge retention following a targeted educational programme on anaemia in pregnancy, HDP and GDM, and their long-term sequelae.

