### Stage 1: Education and Training

A train the trainers programme has been developed for all study staff on the importance of identifying women with a high-risk pregnancy; detecting anaemia, HDP and GDM antenatal and postnatally, and the impact of these conditions on the life-long health of women. The programme also outlines the delivery of the standardised training for CHWs.

The training curriculum for CHWs has been designed to build upon existing CHW training on high-risk pregnancies, and cover key learning objectives in relation to the importance of identification of high-risk pregnant women, with a focus on detection, referral and management of HDP, GDM, and anaemia in pregnancy according to established clinical guidelines (27–31). CHWs will also be taught how to use the SMARThealth Pregnancy mHealth mobile tablet, and provided information on what to do if the technology does not work properly. They will additionally learn the following skills:

Measuring BP using the CRADLE VSA Blood Pressure Monitor (APEC, UK) (32) and interpreting the readings. The CRADLE device is a low-cost semi-automated BP device, specifically designed for low resource settings, charged using an android phone charger, and has been used by CHWs in India (31).Measuring Hb using the handheld TrueHb Hemometer (Wrig nanosystems Pvt. Ltd., 2020) (33) and interpretation of readings.Communication of findings and concerns by ASHA to ANM/primary care doctor, and skills in handover of care between health professionals.

Training will be delivered to ASHAs and ANMs in a series of five participatory learning sessions each of 3-h duration conducted over two and a half days, with a 1-day face-to-face refresher training session after 4 weeks. In between the two training sessions, there will be “hand-holding” in the field by the local study field team, to ensure the ASHAs feel confident using the blood pressure device, haemoglobinometer and the tablet device (see below).

The curriculum for primary care doctors will cover the same areas as for CHWs, however the delivery will be over a half-day of one-to-one training, assuming a degree of baseline knowledge on both educational and training components.

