### Stage 2: The SMARThealth Pregnancy mHealth Platform

The SMARThealth Pregnancy mHealth platform is a smartphone-based application, using an Android operating system, on a seven inch mobile tablet. The application is multi-faceted and includes provision of clinical decision support for ASHAs and primary care doctors regarding interpretation of BP, Hb and blood sugar measurements, grading of severity and appropriate referral information using established clinical guidelines (27–31). Mobile tablets will be provided to ASHAs working in the villages, and to the primary care doctor at the corresponding PHC.

In addition to standard antenatal and postnatal visits, ASHAs in the intervention group will visit the pregnant woman enrolled in the study at home, and perform BP readings, and take a finger-prick Hb test at three different time points:

Once during the last trimester of pregnancy between 28 and 36 weeks' gestation.At 1–2 weeks postpartumAt 6 weeks postpartum

The SMARThealth Pregnancy mHealth platform will have options for the ASHAs to enter the input measurements to generate recommendations based on the woman's history, BP, Hb and blood glucose readings, which will be confidentially uploaded to a patient record using Open MRS software (34) and synchronise to a sister-tablet held by the primary care doctor at the local PHC. All recommendations are based on established country-specific clinical guidelines. Women will be referred to the doctor at the local PHC via the mHealth platform, and provided with a paper referral card. Although women cannot be compelled to see the primary care doctor, they will however be encouraged to attend the PHC after each ASHA visit. The ASHA will accompany the woman for the visit to the primary care doctor or to secondary care as per current standard practise.

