Through the SMARThealth Pregnancy mHealth platform, the primary care doctor will be able to note if the woman is anaemic (and the severity), hypertensive, and/or screen-positive for GDM. The primary care doctor will be guided to repeat these readings if the patient attends the PHC, with access to guideline-based decision support for anaemia, hypertension and GDM as to the next steps in management/and or referral to secondary care. Priority patients (identified to have high-risk pregnancy conditions, and/or outstanding investigations), will have a red traffic light alert and be automatically placed at the top of the priority list when the SMARThealth Pregnancy application is launched on the ASHA and primary care doctor tablets.

Postnatal visits take the same course as the antenatal visit, except the history-taking will involve details of the birth and labour (Postpartum: Week 1 visit), and any further complications (Postpartum: Week 6 visit).

To ensure quality assurance for intervention practises, regular field visits and observations of ASHAs and primary care doctors will be made by the research team and project managers at each study site to ensure compliance to study procedures and the fidelity of the intervention practises. In addition, data collected through the mHealth tablets will be used to monitor visits made and completed by ASHAs and primary care doctors.

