### Stage 3: End of Study Assessment

After the final 6 week postpartum ASHA visit, an independent researcher (not blinded to the intervention) will visit the woman at home and complete an end of study questionnaire, and record BP and Hb readings independently in both the intervention and control groups. This visit will be conducted between 6 and 10 weeks postpartum allowing for convenience of study participants. They will also document if women in the control group had received a 6 week postpartum visit from their ASHA/ANM.

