### Primary and Secondary Outcomes

Primary outcomes relating to feasibility of the intervention include:

Recruitment rates of pregnant participants per cluster per month.Retention rates of participants at 6 weeks postpartum.An overview of the acceptability of the SMARThealth Pregnancy intervention using a qualitative sub-study.

Secondary outcomes include:

Prevalence rates of moderate to severe anaemia, HDP and GDM diagnosed in the study sites.Assessment of fidelity of the intervention by:Proportion of visits conducted in line with intervention protocol.Proportion of visits completed by ASHA (including measurement of Hb and BP) at visits during: (a) third trimester, (b) 1–2 weeks postpartum, (c) 6 weeks postpartum, in the intervention group.Proportion of pregnant women detected, referred, managed, and followed-up, with moderate to severe anaemia, HDP or GDM.Proportion of women receiving their 6 week postnatal check by the ASHA.Clinical outcomes: Mean Hb and mean BP at 6 week postpartum visit.

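### The only quantitative fidelity source named is the ASHA's own tablet record, with no stated check with the woman, and the 6 week visit may be classified from different sources in the two arms

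*Protocol article*

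**What the plan says.** Under Aims and Objectives, the protocol sets the secondary objective "Assess the extent to which the intervention was delivered as planned by CHWs (intervention fidelity"), to be met "by looking at the completeness of the entries into the mHealth tablet and the timing of these entries".

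Under Stage 2, the platform "will have options for the ASHAs to enter the input measurements to generate recommendations", so the worker who makes the home visit also writes its record. The same section plans that "regular field visits and observations of ASHAs and primary care doctors will be made by the research team" for quality assurance, and adds that "data collected through the mHealth tablets will be used to monitor visits made and completed by ASHAs and primary care doctors".

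The fidelity outcomes under Primary and Secondary Outcomes are visit-based. One is the share of visits that followed the protocol. The other is "Proportion of visits completed by ASHA (including measurement of Hb and BP) at visits during" the third trimester, 1–2 weeks and 6 weeks postpartum, in the intervention group. Neither names a data source.

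The Process Evaluation explores delivery qualitatively in a purposive sample from the intervention groups.

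Under Stage 3, an independent, unblinded researcher visits women in both groups at 6 to 10 weeks with a questionnaire. On visit receipt it says: "They will also document if women in the control group had received a 6 week postpartum visit from their ASHA/ANM". The Statistical Analysis section calculates the 6 week visit proportion for both groups.

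**The concern.** There are two linked weaknesses.

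First, the one quantitative source named for fidelity is written by the person whose delivery is being assessed, and the same data are used to monitor her visits. An entry made without a visit or measurement would count as delivered. A visit made while the tablet failed, or entered late, would count as missed or mistimed. The protocol foresees tablet failure, since CHWs will be "provided information on what to do if the technology does not work properly". The tablet record alone cannot tell these cases apart. Over-recording could make poor delivery look like an ineffective intervention, and under-recording could make a technical fault look like poor adherence by the ASHA.

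Second, the 6 week visit proportion is to be calculated in both groups, but independent documentation is stated only for controls. If the intervention figure comes from the tablet, a difference between arms could reflect the source and not the care received.

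**Working it through.** **Passages side by side**

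| Source on delivery | Where | Arm | Gives a proportion? |
|---|---|---|---|
| ASHA tablet entries | Aims and Objectives; Stage 2 | Intervention | Yes |
| Field visits and observation | Stage 2 | Intervention (users of the platform) | None stated: no sampling fraction and no link to an outcome |
| Focus groups and interviews | Process Evaluation | Intervention | No: purposive sample |
| Researcher's note of 6 week visit | Stage 3 | Control only, as stated | Yes |

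So the tablet is the only named source that yields a fidelity proportion for the intervention arm. The one researcher-documented visit item is stated for the other arm.

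**Number of visits**

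The protocol's total reproduces: 4 clusters × 50 women = 200. Assuming one intervention cluster per site, there are 2 × 50 = 100 intervention women and 100 × 3 = 300 scheduled ASHA visits.

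**Illustration of misrecording (all rates assumed)**

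Let t be the true share of visits delivered, s the share of delivered visits that are entered, and f the share of undelivered visits that are entered anyway.

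Recorded fidelity = t·s + (1 − t)·f

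| t | s | f | Recorded |
|---|---|---|---|
| 0.70 | 1.00 | 0.25 | 0.70 + 0.30 × 0.25 = 77.5% |
| 0.70 | 1.00 | 0.50 | 0.70 + 0.30 × 0.50 = 85% |
| 0.70 | 0.90 | 0 | 0.70 × 0.90 = 63% |
| 0.70 | 0.80 | 0 | 0.70 × 0.80 = 56% |
| 0.70 | 0.90 | 0.25 | 0.63 + 0.075 = 70.5% |

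In the last row the two errors nearly cancel: the total looks right while individual visits are misclassified. Only visit-level agreement would show this.

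For scale, the 95% half-width at 70% with n = 100, ignoring clustering, is 1.96 × √(0.7 × 0.3 / 100) = 0.090, or about 9 points. Misrecording of the assumed size can be close to this or exceed it.

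**Consequence for the 6 week comparison**

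Suppose true receipt is 70% in both arms and the researcher classifies controls correctly. If the intervention figure is taken from the tablet, the apparent difference is 77.5 − 70 = +7.5 points in the first row and 63 − 70 = −7 points in the third, with no real difference.

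**Recall at the end-of-study visit**

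For the antenatal visit (28 to 36 weeks, birth at 40 weeks assumed), the shortest recall is (40 − 36) + 6 = 10 weeks and the longest is (40 − 28) + 10 = 22 weeks. For the visit at 1–2 weeks it is 6 − 2 = 4 to 10 − 1 = 9 weeks. For the 6 week visit it is at most 10 − 6 = 4 weeks.

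**The case against.** A reader might infer that the plan measures data entry and not delivery at all, and that delivery in the intervention arm goes unchecked. The documents do not support this:

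- The mHealth platform is one of the two intervention components. Entering history and measurements is what generates recommendations and sends the record to the doctor's tablet. A home visit without an entry did not deliver decision support, so counting it as incomplete is defensible.
- Field observation is planned expressly with fidelity in mind, and tablet data are an addition to it. The article does not say that observations are kept out of the fidelity outcomes.
- The qualitative work asks women and CHWs about delivery after each of the three visits.
- The end-of-study questionnaire is not shown and may already ask intervention women about ASHA visits.
- Fidelity is a secondary outcome in a descriptive pilot, and the article ties no progression threshold to it. Nothing in the documents suggests that false entries occur.

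All of this stands, and it limits the point. Two gaps remain. Neither the observations nor the qualitative work is stated to yield a proportion that could be set against the tablet figure. And Stage 3 states its visit-receipt item for controls only, although the analysis needs it in both groups. If the questionnaire already covers intervention women, the remedy is only to say so and name it as the source.

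**Conclusion.** The point holds in a limited form. The tablet record is a reasonable proxy for delivery, but it comes from the deliverer, no check with the woman is stated, and its error can go either way. The 6 week visit proportion may rest on different sources in the two arms.

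The size is unknown. The 56% to 85% range around a true 70%, and the apparent arm differences of about 7 points, rest wholly on assumed rates and are not estimates. The count of 100 intervention women assumes one intervention cluster per site.

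A reader might go further and infer that delivery should be redefined as a tablet entry confirmed by the woman, over all women enrolled. That does not follow. A visit lost to tablet failure would still count as undelivered, and women lost to follow-up cannot confirm anything. With perfect delivery and an assumed 15% loss, the confirmed rate could not exceed 85%, which mixes retention, a primary outcome in its own right, into fidelity.

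This is a worthwhile, low-cost improvement and not a flaw that undermines the pilot.

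**What to change.** 1. **Stage 3.** Have the researcher ask women in both groups the same item on the 6 week postpartum visit, and use that answer for the two-group proportion in the Statistical Analysis section.
2. **Stage 3, intervention women.** Add one short item per scheduled ASHA visit: did she come, was BP taken, was a finger-prick Hb test done.
3. **Aims and Objectives; Primary and Secondary Outcomes.** Keep completeness and timing of tablet entries. Name the data source for each fidelity outcome. For each of the three visits, report tablet-recorded and woman-reported proportions side by side with their agreement, among women reached at 6 to 10 weeks. Show women not reached as unverified, not as undelivered.

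The cost is a few items in a questionnaire that is already planned, plus one cross-tabulation per visit. No new contact and no change in sample size are needed.

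The woman's report has limits of its own: recall of about 10 to 22 weeks for the antenatal visit, possible confusion with routine visits or with the researcher's own baseline measurements at home, and an unblinded interviewer. Neither source should therefore be treated as the truth, and showing both lets the reader judge.

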## Methods

### Study Design

This is a prospective, parallel, unblinded, cluster randomised controlled pilot study (cRCT). The design was chosen to model and assess study practises including participant recruitment, retention and fidelity of intervention delivery to inform the design of a future definitive trial. The study protocol was developed using the CONSORT 2010 statement extension for randomised pilot and feasibility trials (19). As part of the evaluation process, a qualitative sub-study will be conducted with participants and healthcare workers. This pilot trial was registered with ClinicalTrials.gov (NCT03968952) (20).

